# Get Back, a person-centred digital programme targeting physical activity for patients undergoing spinal stenosis surgery—a study protocol of a randomized feasibility study

**DOI:** 10.1186/s40814-023-01433-9

**Published:** 2024-01-26

**Keywords:** Spine disease, eHealth, Physical activity, Physiotherapy, Feasibility

## Abstract

**Background:**

Spinal stenosis is the most common reason for elective spine surgery, and the cardinal symptom is leg pain and discomfort when walking. Patients with spinal stenosis have a decreased level of physical activity and thereby an increased risk of poor health. Get Back is a person-centred digital programme that strives to support patients being physically active after surgery. The aim is to explore if Get Back, in its present format (referred to as Get Back_feasibility_), is feasible and contributes to detectable change in variables related to intervention content.

**Methods:**

Thirty patients planned for decompression surgery due to central lumbar spinal stenosis who present with low physical activity, pain catastrophizing or fear of movement, will be included in a randomized feasibility study. All patients will be randomly allocated to either Get Back_feasibility_ or usual physical therapy. Get Back_feasibility_ aims to increase the patient’s physical activity level by combining a person-centred and cognitive behavioural approach. It comprises 10 video and telephone sessions led by a physical therapist over 12 weeks (pre/postoperatively). Outcomes are treatment fidelity (treatment dose, adherence, and content), process feasibility (recruitment, intervention use, and acceptability of measurements and intervention), and variables related to the intervention content (steps per day, physical activity level, pain catastrophizing, fear of movement, and general self-efficacy). Treatment fidelity and feasibility data will be assessed during the full study period (12 weeks). Physical activity, physical capacity, and patient-reported outcomes will be assessed digitally at baseline (2 weeks preoperatively) and 11–12 weeks postoperatively. Variables related to the intervention content will be monitored weekly through a digital application. Feasibility data will be analysed descriptively and inferentially using a nonparametric approach, data from repeated measures will be displayed graphically and data from telephone interviews will be analysed using content analysis with a descriptive manifest approach.

**Discussion:**

The results will provide information on whether Get Back in its present format is feasible and can be evaluated for effectiveness in a larger randomized controlled trial, for patients with a low physical activity level and a high fear of movement who are undergoing decompression surgery.

**Trial registration:**

Registered at ClinicalTrails.gov 04/08/2023, registration no. NCT05806593.

**Supplementary Information:**

The online version contains supplementary material available at 10.1186/s40814-023-01433-9.

## Background

Lumbar spinal stenosis (LSS) is the most common indication for surgical treatment in the lumbar spine [1]. LSS often causes neurogenic claudiocation which in turn limits walking ability. The surgical preference for LSS is decompression [2] aiming at relieving pain, and increasing walking ability and health-related quality of life. Studies suggest that patients with LSS are less likely to meet recommendations for healthy physical activity before and after surgery compared to population norms [3, 4]. Physical inactivity before surgery for LSS is associated with less improvement in postoperative disability and pain [5]. Since people who are physically inactive have an increased risk for noncommunicable diseases such as cardiovascular disease, cancers, and diabetes [6], physical activity should be included in pre- and rehabilitation programmes. It is known that people with the lowest levels of physical activity have the largest health-related benefits of increasing their activity [7].

A recent meta-analysis assessing the effect of prehabilitation prior to lumbar spine surgery (LSS included) concluded that there was very low to low certainty for evidence of no additional effect compared to usual care on postoperative physical functioning, pain, and complications [8]. Nevertheless, studies in the meta-analysis included study populations with both high- and low-risk patients, a variety of interventions and the sample sizes were small. One way to reinforce certainty is to target high-risk subgroups, such as people who are deconditioned with low physical activity, in future studies [8]. In addition, a need has been pointed out for studies investigating the combination of pre- and rehabilitation, as the optimal rehabilitation period is still unclear [9, 10].

Previous pre- and rehabilitation programmes for LSS have primarily focused on reducing disability rather than promoting health [11, 12]. A global call suggested health as an overarching strategic approach for people with low back pain [13]. Physical activity is identified as a significant indicator for health and can be used as a valid outcome. To date, outcomes have primarily been evaluated with patient-reported outcome measurements (PROMs) within the research field [14], and it has been questioned how well they capture postoperative physical activity and related health [15].

For patients with lumbar spinal stenosis, the cardinal functional problem is walking, and poorer walking capacity is associated with lower daily step counts [16]. Since steps per day is associated with a progressively lower risk of all-cause mortality up to 6000–8000 steps per day in people over 60 years of age [17], walking is recommended directly after surgery. Increased walking time and steps per day directly after surgery are associated with reduced pain and opioid use, as well as improved functioning 6 and 12 months after lumbar spine surgery due to a lumbar degenerative condition including LSS [18, 19]. In the current study, steps per day will be the main focus.

Common reasons, as described by patients, for not engaging in physical activity post-surgery are sedentary habits, persistent pain, and fear of reinjury of the spine [20]. There is conflicting evidence regarding the association between preoperative fear of movement/pain catastrophizing and postoperative pain and disability [21–23], and little is known about how fear of movement interacts with physical health outcomes such as physical activity. In a prior study, we found that preoperative fear of movement was a significant predictor of sedentary behaviour at 6 and 12 months after lumbar fusion surgery. A few studies have indicated that pain-related fear of movement is associated with fewer steps per day in patients with degenerative lumbar disease, including LSS [16, 24].

Moreover, it is suggested that “one size does not fit all” [25], and a person-centred approach is recommended [13]. Person-centred care (PCC) has been shown to increase patients’ levels of self-efficacy in other pain conditions [26]. Therefore, PCC will be a key component of the Get Back programme. Get Back comprises the further development of a previously evaluated person-centred prehabilitation programme including a cognitive behavioural approach that promoted physical activity for patients with chronic low back pain undergoing lumbar fusion surgery [27]. In our prior prehabilitation study, physical activity did not improve over time, despite significantly improved self-reported functioning and objectively measured physical capacity. These findings have an impact on the current understanding of the long-term effects of prehabilitation and of future research, which should focus on programmes promoting physical activity both before and after lumbar spine surgery to decrease the risk of long-term adverse health outcomes (Kemani et al. Long-term follow-up of a Person-Centred Prehabilitation Program Based on Cognitive-Behavioural Physical Therapy for Patients Scheduled for Lumbar Fusion Surgery. *Submitted*). Get Back will be delivered in an eHealth format. It has previously been revealed that patients decline participation in face-to-face interventions due to geographical barriers [27]. The use of eHealth can support their availability for rehabilitation [28].

Due to the argumentation above, Get Back is designed in the format of a person-centred digital programme that aims to support high-risk patients in being physically active after decompression surgery for spinal stenosis. Prior to performing a full-scale randomized controlled trial, we will conduct a feasibility trial to assure and refine the evaluation design and the intervention itself, as recommended by The Medical Research Council [29]. The current version of the intervention, tested in the feasibility study, will be referred to as Get Back_feasibility_. Here we present the protocol of a study with the objective of evaluating whether Get Back_feasibility_ in combination with decompression surgery can provide a detectable change in variables related to the intervention content and to evaluate the treatment fidelity as well as feasibility in terms of the trial procedure, intervention use, and acceptability in patients identified with a low physical activity level and pain catastrophizing or fear of movement.

## Methods

### Research questions

All research questions below are formulated in the PICO format and concern patients with a low physical activity level and high pain-related catastrophizing and/or fear of movement receiving decompression surgery for lumbar spinal stenosis.

#### Research questions pertaining to outcomes relating to the Get Back_feasibility_ content

Do the assessments preoperatively and at 12-week follow-up of steps per day, physical activity and pain catastrophizing, fear of movement and general self-efficacy provide tentative information as to the efficacy of the Get Back_feasibility_ intervention?Do the weekly assessments of single-item questions aiming to measure steps per day, physical activity and aspects of pain catastrophizing, fear of movement and self-efficacy provide additional information regarding the efficacy of the Get Back_feasibility_ intervention, trajectories of change and interrelations between variables?

#### Research questions in relation to treatment fidelity of the Get Back_feasibility_ intervention

(3)Is the treatment dose and content of Get Back_feasibility_ delivered as intended?(4)Does the physical therapist delivering the Get Back_feasibility_ intervention adhere to a person-centred approach?

#### Research questions in relation to process and resource feasibility

(5)What percentage of patients planned for decompression surgery for lumbar spinal stenosis meeting inclusion criteria are eligible after the screening procedure?(6)What are the reasons for declining participation in the study or dropping out?(7)Is the screening questionnaire measuring physical activity level able to detect patients with a low level of physical activity compared to accelerometer data at baseline?(8)How many of the planned sessions of the Get Back_feasibility_ intervention do patients of the intervention group attend?(9)Did the study participants and physical therapists (PT) in the study find the digital format, Get Back_feasibility_ intervention, and outcome measures relevant and usable?(10)Is the Get Back_feasibility_ treatment safe (type and frequency of adverse events)?(11)What is the response rate of the used PROMs and to what extent are physical tests completed? If they are not completed, what are the reasons?

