### Participants and study settings

Participants will be recruited from two private spine clinics with referrals from the regions, in Sweden: Capio Spine Center Göteborg and Ryggkirurgiskt centrum (RKC), Sophiahemmet, Stockholm. Inclusion criteria: (i) patients planned for decompression surgery (without concomitant fusion) due to lumbar central spinal stenosis; (ii) patients > 18 years of age. Exclusion criteria: (i) patients with malignancy, severe neurological -or rheumatological disease, idiopathic scoliosis, or isthmic spondylolisthesis; (ii) persons unable to understand written information and communicate in Swedish; and (iii) patients with untreated/unstable heart disease that prohibits physical capacity tests. For patients meeting the inclusion criteria, the following screening criteria should also be fulfilled: (i) low level of physical activity (i.e. persons who do not meet WHO’s physical activity recommendations of a weekly minimum of 150 min of physical activity of moderate intensity), and (ii) higher levels of fear of movement or pain catastrophizing, equivalent with scores ≥ 37 on the Tampa Scale of Kinesiophobia (TSK) [33] and ≥ 30 on the Pain Catastrophizing Scale (PCS) [34].

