### Recruitment

All patients will have a consultation with a spine surgery specialist who based on anamnesis and clinical and radiological findings will determine the diagnosis and give recommendations regarding the treatment regime(s). Patients planned for surgery and eligible for the study will be identified by an independent local recruiter who will contact the patients by phone, provide oral study information and screen for risk factors. The independent recruiter will also ascertain whether the participant has the required technology (smartphone, computer, or tablet with a camera, as well as an internet or mobile network connection). If the screening criteria are fulfilled, the patient will be asked for participation and oral informed consent. A digital baseline assessment will be scheduled with an independent observer (physical therapist) approximately 2 weeks before surgery. Before the baseline assessment, written informed consent will be obtained digitally. An overview of the study flow is seen in Fig. 1.

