### Procedure

At baseline (approximately 2 weeks preoperatively) and follow-up (11–12 weeks postoperatively), physical activity, physical capacity and PROMs will be assessed. For physical activity, once the patient has agreed to participate in the study, the study coordinator will mail an accelerometer (ActiGraph GT3X + ; ActiGraph, Pensacola, FL, USA) and written user information to the participant for a 7-day assessment. Thereafter, an independent observer will collect demographic/clinical data and conduct physical capacity tests via video. In case of adverse events during video assessments, the independent observer has been instructed to contact medical care immediately if the patient becomes acutely ill or guide the patient to seek medical care if more of a subacute nature. The patient will fill out the PROMs through a secure digital platform (the application BASS, Karolinska Institutet, Stockholm, Sweden). During the intervention, the participants will also fill out weekly repeated measurements in BASS. These weekly measures will include twelve one-item questions addressing physical activity levels, fear of movement, catastrophizing, self-efficacy, and steps per day. Reminders will be sent out automatically via text message if the participant has forgotten to fill in a questionnaire in BASS. At the end of the study, a telephone-based semistructured interview, with all intervention participants, regarding feasibility aspects and participation will be conducted by the study coordinator. Feasibility data will be collected continuously during and at the end of the study period (see Fig. 3).

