#### Process and resource feasibility

Process feasibility [68] will be administered by the following variables: recruitment, intervention use, and acceptability. Recruitment aspects include the percentage of patients eligible after the screening procedure, as well as the reasons for declining participation or dropping out of the study. Patients who withdraw from the study will also be asked if data collected up until the time point of the withdrawal can be used in the study. Intervention use will be calculated as the ratio of the number of completed treatment sessions versus the number of planned sessions. Acceptability with the digital format and intervention will be evaluated using a semistructured interview at the end of the intervention where all intervention participants will be asked about their experience. The Study PT will answer a questionnaire with specific questions about their experience with the intervention. Furthermore, all study participants and assessors will be asked to complete study-specific questionnaires about their thoughts on the digital data collection format (including both PROMs and physical capacity tests) and using the accelerometer. The self-reported physical activity level at screening will be compared with accelerometer data at baseline to evaluate the chosen questionnaire’s ability to detect patients with a low level of physical activity. Treatment safety will be addressed by the type and frequency of possible adverse events during the intervention collected by the Study PT after each session.

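### Research question 7: the baseline accelerometer data can confirm low activity among patients the questionnaire selected, but cannot show how well the questionnaire detects low-active patients

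*Protocol article*

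**What the plan says.** All references are to the protocol article.

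- **The question.** Under Research questions in relation to process and resource feasibility, item 7 asks: "Is the screening questionnaire measuring physical activity level able to detect patients with a low level of physical activity compared to accelerometer data" at baseline.
- **The analysis.** Under Process and resource feasibility: "The self-reported physical activity level at screening will be compared with accelerometer data at baseline". The stated purpose is to judge how well the questionnaire identifies low-active patients.
- **Selection.** Under Participants and study settings: "For patients meeting the inclusion criteria, the following screening criteria should also be fulfilled: (i) low level of physical activity". Low means not reaching the WHO minimum of 150 minutes of moderate activity per week. Raised fear of movement or catastrophizing is a further screening criterion.
- **Invitation.** Under Recruitment: "If the screening criteria are fulfilled, the patient will be asked for participation and oral informed consent".
- **Measurement.** Under Procedure: "once the patient has agreed to participate in the study, the study coordinator will mail an accelerometer".
- **Reporting.** Statistical methods plans minutes per week in each intensity category, step bands, and the proportion reaching the WHO recommendation. An accelerometer record counts as valid with at least 10 hours of wear on at least 4 days.

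**The concern.** Whether a screening tool detects a condition depends on the cases it misses as well as on the cases it flags. Here the flag is itself an entry condition, and the reference measurement is taken only after entry. Every patient in the comparison has therefore been flagged already. Low-active patients whom the questionnaire classed as sufficiently active leave the study before anyone can learn of them.

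What is at stake is the conclusion drawn from question 7. A high share of confirmed patients, reported in the terms the protocol uses, would be a statement about detection that the data cannot carry. The Discussion says that the study procedure will be revisited before a full trial, and screening is part of that procedure.

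**Working it through.** **1. The plan's own figures.** The protocol gives no target or expected value for question 7. The only number that bears on it is the sample size, 15 + 15 = 30, which is the most patients who can have both measures. The wear-time rule may lower that number.

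**2. Which cells the design fills.**

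| Questionnaire at screening | Accelerometer: low | Accelerometer: not low |
|---|---|---|
| Low (may be invited) | TP, measured | FP, measured |
| Not low (not invited) | FN, never measured | TN, never measured |

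- Positive predictive value = TP / (TP + FP): estimable.
- Sensitivity = TP / (TP + FN): FN unknown.
- Specificity = TN / (TN + FP): TN unknown.
- Negative predictive value = TN / (TN + FN): both unknown.

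A larger sample would fill only the top row.

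**3. Precision of what is estimable.** The confirmed counts are assumptions. Intervals are exact (Clopper-Pearson).

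- 24 of 30: 80%, 95% CI 61% to 92%.
- 19 of 24, if only 24 records are usable: 79%, 95% CI 58% to 93%.

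**4. What the same data leave open.** Keep TP = 24 and FP = 6. Assume 30 unmeasured screen-negative patients, a share q of whom are low-active, so that sensitivity = 24 / (24 + 30q).

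| q (assumed) | Calculation | Sensitivity |
|---|---|---|
| 10% | 24 / 27 | 89% |
| 40% | 24 / 36 | 67% |
| 70% | 24 / 45 | 53% |

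With q left free, the limits depend on the assumed number m of unmeasured patients:

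| m (assumed) | Lowest sensitivity | Highest specificity |
|---|---|---|
| 10 | 24 / 34 = 71% | 10 / 16 = 63% |
| 30 | 24 / 54 = 44% | 30 / 36 = 83% |
| 60 | 24 / 84 = 29% | 60 / 66 = 91% |

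In each row sensitivity can reach 100% and specificity can fall to 0%.

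**5. A high confirmed share need not mean discrimination.** With prevalence p, sensitivity s and specificity c, the positive predictive value is ps / [ps + (1 − p)(1 − c)]. If c = 1 − s, the tool carries no information and the expression reduces to p. So if 80% of all screened patients were low-active (assumed), a tool with s = c = 50%, or with s = 90% and c = 10%, would also give 80%.

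**6. Limit of the illustration.** Steps 4 and 5 treat the enrolled patients as standing for all questionnaire-positive patients. Those who declined, or who failed the fear or catastrophizing criterion, were also flagged but are not counted. The figures show the width of the gap and do not estimate this questionnaire's sensitivity.

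**The case against.** The strongest reply is that the protocol never promises sensitivity, specificity or a two-by-two table. It says under Research questions that all its questions "concern patients with a low physical activity level and high pain-related catastrophizing and/or fear of movement". Read that way, question 7 asks only whether the patients selected by the questionnaire are truly low-active, and the baseline data answer that. Part of this stands. The confirmed share is a legitimate feasibility result, and a reader who infers that question 7 cannot be answered at all goes too far. But both places that describe the comparison frame it as detection, which the selected sample cannot show.

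Three other routes to screen-negative data were checked.

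- The abstract's looser list of entry conditions might suggest that some active patients enter. Participants and study settings, Research questions and the end of the Background all require low activity together with fear or catastrophizing.
- Question 5 counts the patients who are eligible after screening, but it brings no accelerometry on those excluded.
- Self-report and accelerometry are both repeated at 11–12 weeks, where all four cells could occur. Those patients all screened low at entry, have had surgery, and in the intervention group have been monitoring their own steps. Screening was by telephone, whereas follow-up questionnaires are completed in an application. A table at that visit cannot show what the preoperative screen missed.

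Two stronger readings are not supported either. A reader might infer that the accelerometer reference is ambiguous because step bands are reported. Statistical methods also plans the WHO proportion, which matches the entry criterion, and nothing makes the step bands the reference for question 7. A reader might also infer that question 7 decides whether the questionnaire is kept for the full trial. The Discussion says only that content and procedure will be revisited, and no decision rule is tied to this result.

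**Conclusion.** The point holds in a limited form. As worded, question 7 and its description under Process and resource feasibility claim more than the design can deliver. With no screen-negative patient measured, sensitivity, specificity and negative predictive value are not identifiable, and no later analysis can recover them. This conclusion follows from the entry, invitation and mailing steps alone and needs no assumed number.

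The size of the gap can only be illustrated. Under the stated assumptions, one observed result of 80% confirmed fits a sensitivity from 89% down to 53%.

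This should be fixed but does not threaten the trial. It concerns one of eleven research questions, is to be reported descriptively, and leaves randomization, the other outcomes and the sample size untouched.

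**What to change.** Restate question 7 and the matching sentence under Process and resource feasibility along these lines: among enrolled patients whose screening self-report was low, the proportion whose valid baseline accelerometer record shows less than 150 minutes per week of at least moderate activity, with an exact 95% confidence interval. This is the threshold of the entry criterion, and the WHO proportion is already planned under Statistical methods.

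Add that the result applies only to consenting patients who also met the fear or catastrophizing criterion. Make no claim about detection, sensitivity or missed low-active patients.

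A cross-tabulation of the two-item self-report against the accelerometer at 11–12 weeks may be added as exploratory agreement in postoperative patients. It should not be presented as evidence on the preoperative screen. Its relevance also assumes that the screening instrument is the two-item questionnaire listed under Physical activity level, which the screening sections do not state.

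The cost is two reworded sentences and, if wanted, one extra table. No new patients or measurements are needed. The price is a narrower claim.

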#### Physical activity level

Objectively measured by a digital triaxial accelerometer (ActiGraph) via the variables, steps per day, time spent in light physical activity, moderate to vigorous physical activity (MVPA), and time spent sedentary [54].Self-reported physical activity with a two-item questionnaire from the National Board of Health and Welfare in Sweden [55].

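### RQ7 tests the activity questionnaire only by setting the recruitment phone answer against later accelerometry, so questionnaire error cannot be told apart from real change; the baseline self-report should be compared as well

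*Protocol article*

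**What the plan says.** In the protocol article, RQ7 (under process and resource feasibility) asks whether the screening questionnaire is "able to detect patients with a low level of physical activity compared to accelerometer data at baseline". The outcome section on process and resource feasibility fixes the pair: "The self-reported physical activity level at screening will be compared with accelerometer data at baseline". The stated purpose is to evaluate how well the chosen questionnaire finds low-active patients.

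The order of events comes from two other sections. Under Recruitment, screening is done by a local recruiter "who will contact the patients by phone, provide oral study information and screen for risk factors". Patients who pass are asked to take part, and "A digital baseline assessment will be scheduled with an independent observer (physical therapist) approximately 2 weeks before surgery". Under Procedure, "once the patient has agreed to participate in the study, the study coordinator will mail an accelerometer" for a 7-day recording.

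A second self-report appears to be available. The physical activity outcome set lists "Self-reported physical activity with a two-item questionnaire from the National Board of Health and Welfare in Sweden" next to the accelerometer, and Procedure says that at baseline and follow-up "physical activity, physical capacity and PROMs will be assessed". The plan for RQ7 does not mention that baseline answer.

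**The concern.** The answer under test is taken at a phone call. The reference measurement starts later, by an interval that the article neither states nor limits. Everyone with a reference measurement got there by giving a low answer at the call. If the accelerometer then shows a patient above the threshold, there are three explanations: the questionnaire misclassified the patient, the patient's activity really changed, or a temporarily low value moved back towards the patient's usual level. The planned pair gives one disagreement rate that mixes all three.

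The explanations lead to different actions. A poor questionnaire calls for a different instrument; change between the call and baseline calls for screening closer to baseline. The Discussion says that content and study procedure will be revisited before the full trial, so it helps if RQ7 can point to one or the other. The error can run either way: a rise in activity makes a good questionnaire look poor, and a fall makes a poor one look good.

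**Working it through.** The plan attaches no figure to RQ7, so there is nothing to reproduce. The check has two parts.

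**1. Timing, from the text.**
- Questionnaire answer: recruiter's phone screen, before consent (Recruitment).
- Reference: device mailed after agreement, worn 7 days, part of a baseline about 2 weeks before surgery (Procedure, Recruitment).
- Interval between them: not stated. Recall period of the questionnaire: not stated.
- Selection: only patients who report less than 150 minutes of moderate activity per week, and who also meet the fear or catastrophizing criterion, proceed to the device.
- Self-report at baseline: listed in the physical activity set, which is assessed at baseline. Its exact timing relative to the wear week is not given.

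So the phone answer precedes the wear week, while a self-report close to the wear week is in the assessment set but not used for RQ7.

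**2. What change would do (illustration; every input here is an assumption).**

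Let PPV be the share of screened-in patients who are truly low-active at the call, c the share of those who are no longer low in the wear week, and g the share moving the other way. Then

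apparent agreement = PPV × (1 − c) + (1 − PPV) × g.

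With PPV = 0.90 and g from 0 to 0.20:

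| c | Apparent agreement | Shift from 0.90 |
|---|---|---|
| 0 | 0.90 to 0.92 | 0 to +2 points |
| 0.05 | 0.855 to 0.875 | −4.5 to −2.5 |
| 0.10 | 0.81 to 0.83 | −9 to −7 |
| 0.20 | 0.72 to 0.74 | −18 to −16 |

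For example, with c = 0.10 and g = 0: 0.90 × 0.90 = 0.81. When self-report and accelerometer cover the same period, c = g = 0 and 0.90 stays 0.90.

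Week-to-week variation alone gives a c above zero. Suppose an error-free questionnaire that describes one particular week, normally distributed (transformed) activity, a share p of candidates below the threshold, and correlation r between true activity in the two weeks. With z the p-quantile of the standard normal and Φ₂ the bivariate normal distribution function, the share low in the first week but not in the second is 1 − Φ₂(z, z; r)/p:

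| p | r | Share no longer low | Of 30 |
|---|---|---|---|
| 0.50 | 0.6 | 29.5% | 8.9 |
| 0.50 | 0.9 | 14.4% | 4.3 |
| 0.70 | 0.7 | 15.6% | 4.7 |
| 0.85 | 0.6 | 9.7% | 2.9 |
| 0.85 | 0.9 | 4.9% | 1.5 |

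If mean activity also falls by 0.3 SD before the wear week, 15.6% becomes 8.4%. The direction therefore depends on what happens during the wait.

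**Sampling error.** The Wilson 95% interval for 27 of 30 is 0.744 to 0.965, and for 22 of 24 it is 0.742 to 0.977. Shifts from c up to about 0.10 (apparent agreement 0.81 to 0.83) lie inside these intervals. An interval shows sampling error, however; it does not show this bias.

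**The case against.** The strongest defence is that the planned comparison fits the question. The recruiter selects on the phone answer, and what matters to a trial of low-active patients is whether those selected are low-active at entry. Change between call and baseline is then part of how well screening works. This stands. A reader might infer that the screening comparison is wrong and should give way to the baseline one; the document does not support that.

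Three other tempting readings also go too far:

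- **That the two measures describe different weeks.** The recall period is not given. If the questionnaire asks about usual activity, the two-week model above does not apply as written. The gap may also be short, since the device is mailed once the patient agrees. The study-flow and schedule figures, which might show it, were not available for this review.
- **That RQ7 decides whether the questionnaire is kept or replaced.** No such rule is attached to it. Feasibility data are to be reported descriptively, and nothing says that disagreement will be read as questionnaire error.
- **That 5% to 30% of patients will be falsely counted as errors.** That range follows arithmetically from assumed correlations and prevalences, none of which is in the document. Its top needs only half of candidates to be low-active, whereas the Background describes these patients as less likely than the population to meet activity recommendations.

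It can also be said that the baseline answer, if given after wearing a device, may be better informed than the phone answer and so flatter the questionnaire, and that the article does not say the two questionnaires are the same. Both are fair. They are reasons to add the second comparison rather than substitute it, and to state the assumption. None of this removes the core point that the single planned pair cannot attribute a disagreement to a cause.

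**Conclusion.** The concern holds in a limited form. RQ7 as planned is a legitimate check of the selection step, but on its own it cannot distinguish a misclassifying questionnaire from real change or regression to the mean. The size cannot be derived from the document: under assumed inputs it runs from negligible to 18 percentage points of agreement, and shifts of up to about 10 points would be hard to see at n = 30. The point is therefore a cheap gain in interpretability, not an error that invalidates RQ7.

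It rests on two inferences: that the two-item questionnaire, the only activity questionnaire the article names, is the screening form; and that it is completed at baseline, as the outcome list and Procedure together imply.

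**What to change.** In the process and resource feasibility section:

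1. Keep screening self-report against baseline accelerometry as the check of the selection step.
2. Report the days between the phone screen and the start of the wear week, for example as median and range.
3. Add a comparison of the self-report collected at baseline with the same baseline accelerometer data, using the same definition of low activity.
4. State how the two results will be read together. Disagreement in both points to the questionnaire; disagreement only in the first points to change between screening and baseline. These are pointers, not proof, because the baseline answer may be better informed after wearing the device.
5. Name the screening form. If it is not the two-item questionnaire, the added comparison does not test the screening form unless that form is also completed at baseline.

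The cost is a few sentences, one date difference and one more descriptive table, from data the plan already appears to collect. One limit remains: patients who screen as sufficiently active never wear the device, so neither comparison can estimate the sensitivity of the phone screen, and the report should say so.
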